### Data Analysis

Descriptive summary statistics will be reported using means and standard deviations, with median values as indicated for nonparametric data. The primary analysis will use a generalized linear model to examine the effect of treatment, time (follow-up at 6 and 12 months), and the interaction between treatment group and time. Values at baseline will be used as a covariate in this analysis. Secondary analyses will include adjustment for other baseline variables including age, sex, forced expiratory volume_
**1**
_, and exacerbations. The generalized linear model creates a working covariance matrix for the model parameters that deals with missing data, including patients who do not complete all follow-up measures. The model uses all data in calculating a net effect of intervention versus control at 12 months and an estimate of precision (95% confidence interval) at that final follow-up. This analytic strategy will be used for all continuous variables that are primary or secondary measures of outcome (ie, 6MWD, CRQ domains, CSES, DASI, chair stand test). Data will be analyzed using the Statistical Package for the Social Sciences, version 22.0, with significance set at *P*<0.05.

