### Allocation

A computer-generated randomization schedule using variable block size will be created. A member of the research team will consecutively randomize participants using sealed, opaque envelopes. Randomization will be stratified by the use of supplemental oxygen to minimize the impact of this factor, as it has been shown to influence the response to PR [19] and improve the total distance achieved during the 6-minute walk test (6MWT) by 12 to 59 m [20,21].

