#### Sample Size Calculation

Sample size calculations are based on the primary outcome measure, the 6MWT. We calculated sample size using a paired samples t-test. As the repeated measures analysis of the variance will be a more powerful analysis than a t-test, our sample size is a conservative estimate. Furthermore, as we will use baseline scores as a covariate in our planned analysis, we will be using within participant variability as our error (and not within participant variability), making our estimate even more conservative. A sample size estimation based on the knowledge of the differences in 6MWD that represent a clinically important difference (54 m and standard deviation of 86 m [15]), type I error of 0.05 and a power of 80%, revealed the need for a sample size of 40 in each group for a total of 80 participants. From our previous experience in this population, we estimate the rates of noncompliance and loss to follow-up to be 15% to 20% (8-10 participants per group). Therefore, we will aim to recruit 100 participants.

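### The primary 6MWD model omits supplemental oxygen use, the only named stratification factor, so the reported standard error can be slightly too large

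*Protocol article*

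**What the plan says.** Allocation names a single stratifier and its purpose: "Randomization will be stratified by the use of supplemental oxygen to minimize the impact of this factor". It gives two reasons: oxygen use influences the response to pulmonary rehabilitation (PR), and it can "improve the total distance achieved during the 6-minute walk test (6MWT) by 12 to 59 m".

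Data Analysis then sets out the model: "The primary analysis will use a generalized linear model to examine the effect of treatment, time (follow-up at 6 and 12 months") and the treatment-by-time interaction. It adds: "Values at baseline will be used as a covariate in this analysis". No other covariate is named for the primary analysis.

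For the adjusted analyses it says: "Secondary analyses will include adjustment for other baseline variables including age, sex, forced expiratory volume", followed by exacerbations. Oxygen use is not named there, but the list is introduced as examples and is not closed. The same analytic strategy is applied to the CRQ domains, CSES, DASI and the chair stand test.

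**The concern.** When allocation is stratified on a prognostic factor, the arms are balanced on it and the treatment estimate varies less from trial to trial. A model that leaves the factor out keeps the between-stratum variation in its residual. The reported standard error can then exceed the true sampling variability: the confidence interval is somewhat too wide and the test rejects somewhat less often than 5% under the null.

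The article judged oxygen use important enough to control by design and lists covariates at two levels of analysis, yet it does not carry the factor into the primary model. What is at stake is a little precision in the reported interval. Bias is not in question. The size depends on how much of the oxygen effect remains once baseline 6MWD is in the model.

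**Working it through.** **Inputs from the article.** Oxygen effect on walk distance d = 12 to 59 m (Allocation); "54 m and standard deviation of 86 m" (Sample Size Calculation); 40 per group (same section); baseline value as covariate (Data Analysis).

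**Assumptions, not in the article.** Oxygen share p = 10% to 50%; within-stratum correlation of baseline with follow-up 6MWD ρ = 0.5 to 0.9; d taken as the difference in mean 6MWD between strata, equal at baseline and follow-up; 86 m taken as the total SD. A single follow-up time stands in for the 12-month contrast.

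**1. The plan's own figure.** The two-sided, two-sample formula gives n = 2 × (1.960 + 0.842)² × (86/54)² = 39.8, so 40 per group, with power 80.2%. This matches the article, which "revealed the need for a sample size of 40 in each group for a total of 80 participants". Allowing 20% loss, 80/0.80 = 100. The formula takes no credit for stratification or baseline adjustment, and the standard error it implies is 86 × √(2/40) = 19.23 m.

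**2. Standard error with and without oxygen.** The between-stratum variance is V_b = p(1 − p)d² and the within-stratum variance is V_w = 86² − V_b.
- Model with baseline and oxygen: residual variance V_w(1 − ρ²).
- Model with baseline only: residual variance 86² − (ρV_w + V_b)²/86².
- Excess = square root of (second ÷ first), minus 1.

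Largest case (d = 59, p = 0.5, ρ = 0.5):
- V_b = 0.25 × 3481 = 870.25 and V_w = 7396 − 870.25 = 6525.75.
- With oxygen: 6525.75 × 0.75 = 4894.3.
- Without oxygen: 7396 − (3262.9 + 870.25)²/7396 = 5086.3.
- Ratio 1.0392, square root 1.0194, an excess of 1.9%. At 40 per group the standard error is 15.95 m against 15.64 m.

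| Shift d | Oxygen share | No baseline covariate | ρ = 0.5 | ρ = 0.7 | ρ = 0.9 |
|---|---|---|---|---|---|
| 12 m | 10% | 0.09% | 0.03% | 0.02% | 0.00% |
| 12 m | 50% | 0.24% | 0.08% | 0.04% | 0.01% |
| 59 m | 10% | 2.19% | 0.70% | 0.37% | 0.11% |
| 59 m | 25% | 4.73% | 1.46% | 0.78% | 0.23% |
| 59 m | 50% | 6.46% | 1.94% | 1.03% | 0.31% |

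The third column describes a model that this trial does not plan. The last three describe the one it does.

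**3. Simulation.** Stratified allocation, 80 patients, no dropout, no treatment effect, 8000 runs. The Monte Carlo error on a 5% rejection rate is √(0.05 × 0.95/8000), about 0.24 percentage points. With d = 59, p = 0.5, ρ = 0.7:
- Without oxygen: mean reported standard error 13.09 m, actual SD of the estimate 13.15 m, type I error 4.9%.
- With oxygen: 12.96 m, 13.16 m, 5.1%.

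The estimate varies equally under both models, so the balance is retained. The two rejection rates cannot be told apart.

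**4. If oxygen also predicts change after baseline.** Adding an assumed further 30 m oxygen effect at follow-up to the case in step 3:
- Without oxygen: mean reported standard error 13.92 m, actual SD 13.15 m, type I error 3.7%.
- With oxygen: 12.96 m, 13.01 m, 4.9%.

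As an outer bound, suppose that the whole 59 m remained after baseline adjustment and that 86 m is the within-stratum SD. The excess is then √(1 + p(1 − p)59²/[86²(1 − ρ²)]) − 1. This is 2.8% at p = 0.1, ρ = 0.5 and 10.9% at p = 0.5, ρ = 0.7.

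**The case against.** The strongest reply is that baseline adjustment already does most of the work. An oxygen effect on test distance that is the same at baseline and follow-up is carried by baseline 6MWD. An effect on the response to PR is largely carried too: patients have completed PR before enrolment (Participants) and baseline is measured after PR (abstract, Methods). Both reasons given for stratifying therefore act largely through a covariate that is in the model. This stands, and it is why the likely excess is about 0% to 2%. It does not exclude a different course in oxygen users over the following 12 months, but the article neither states nor sizes such an effect.

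Three further points stand. The 12 to 59 m is the effect of using oxygen on test distance, not a documented difference between strata, so using it that way is an assumption. The secondary covariate list is open-ended. And the article links oxygen use to PR response and walk distance only, so no precision loss is shown for CRQ, CSES, DASI or chair stand; including the stratum there is for consistency with the design.

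A reader might infer that the precision gained by stratifying is thrown away, or that the standard error is up to 6.5% too large and the type I error 3.7% from the level shift alone. The documents do not support either. The balance stays in the estimate. Those two figures (1/√(1 − 870.25/7396) = 1.065; 1.96 × 1.065 = 2.09, two-sided P = 0.037) belong to an analysis without the baseline covariate.

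**Conclusion.** The point holds for the primary model: the one named stratifier is absent from it. For the secondary adjusted analysis, the most that can be said is that oxygen use is not named; a reader might conclude that neither analysis will include it, but the wording does not settle that.

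The consequence is small and conservative. The estimate is unbiased and balanced by design, and the reported standard error is about 0% to 2% too large under the assumed stratum difference, oxygen share and correlation. A larger excess needs oxygen use to predict change after baseline; the 3.7% type I error rests on an assumed 30 m. Every baseline-adjusted standard error in steps 2 and 3, and the 13.92 m in step 4, is below the 19.23 m behind the sample size, so 40 per group and 80% power are unaffected. This is an inexpensive improvement that brings the analysis into line with the design; it does not correct an invalid analysis.

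**What to change.** Prespecify the baseline oxygen stratum used for randomisation (yes/no) as a fixed covariate in the primary 6MWD model and, for consistency with the design, in the parallel models for the CRQ domains, CSES, DASI and chair stand test. Keep age, sex, FEV1 and exacerbations for the secondary adjusted analysis. If the stratum is to be left out, say why.

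The cost is one degree of freedom per model and no new data, since the factor is recorded at randomisation. The Results section describes recruitment as under way with about half the participants enrolled, so at that stage the change can be fixed before any outcome analysis. Added after the data are seen, it would be post hoc.

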## Introduction

### Background

Chronic obstructive pulmonary disease (COPD) is a leading cause of death across the world [1] and will become increasingly common with an aging population. The prevalence of COPD increases with age and is highest in individuals aged 65 years and over [2], with a current prevalence of 20% in this age group [3]. The natural course of COPD is that of progressive worsening of airflow limitation, repeated exacerbations, respiratory failure, and premature death. Among the major chronic illnesses in Canada, COPD accounts for the highest rate of hospital admissions [4]. Coupled with the knowledge that COPD is a common and costly condition [5], long-term strategies to improve health outcomes and prevent functional decline are likely to result in a decrease in health resource usage [6].

It is well established that pulmonary rehabilitation (PR) for those who suffer from COPD results in short-term improvements in dyspnea, exercise capacity, and health-related quality of life (HRQL). However, benefits achieved through PR tend to diminish over time [7,8], often to the point that outcomes return to preintervention levels within 12 months [9,10]. Nonadherence to a maintenance home exercise program is a key factor associated with the decline in outcomes [9,11], with a 50% reduction in adherence only 9 months after completion of intensive rehabilitation, according to patient self-report [11]. While patients are encouraged to adhere to their home exercise program upon discharge, many have difficulty maintaining their exercise routine after the transition from a hospital-based rehabilitation setting to a community setting. The benefit of rehabilitation is further diminished as patients who develop acute exacerbations struggle to return to their previous level of exercise without professional guidance [11].

Consequently, there is a growing interest in developing innovative follow-up strategies to promote long-term exercise maintenance. Supervised exercise programs delivered following PR appeal to individuals with COPD [12] and are more effective than usual care for preserving exercise capacity in the medium term [13] Studies that have examined post-rehabilitation maintenance programs in patients with COPD have not shown consistent positive effect [14,15]. The optimal method for preventing functional decline following PR remains unclear, especially in individuals with moderate and severe COPD who experience frequent exacerbations.

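### The missing-data sentence credits the working covariance matrix with protection it does not give; the primary model and its missingness assumption should be named

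*Protocol article*

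**What the plan says.** The Data Analysis section of the protocol article sets out the model: "The primary analysis will use a generalized linear model to examine the effect of treatment, time (follow-up at 6 and 12 months"), with a treatment-by-time interaction. On baseline it adds: "Values at baseline will be used as a covariate in this analysis". It then makes a claim about incomplete follow-up: "The generalized linear model creates a working covariance matrix for the model parameters that deals with missing data", and it counts participants with incomplete follow-up among those covered. It continues: "The model uses all data in calculating a net effect of intervention versus control at 12 months", with a 95% confidence interval. The same strategy covers the 6-minute walk distance and every continuous secondary outcome. No covariance structure and no assumption about the missingness mechanism is stated.

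The Sample Size Calculation section anticipates attrition: "we estimate the rates of noncompliance and loss to follow-up to be 15% to 20"%. It describes the analysis under another name: "As the repeated measures analysis of the variance will be a more powerful analysis than a t-test".

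**The concern.** The article does not leave missing data to a later document. It names a mechanism and says that the mechanism handles the problem, and that mechanism is misdescribed. In an estimating-equation analysis the working covariance affects efficiency and the weight each visit receives. Without further weighting or a correct covariance, such an analysis is not in general protected when dropout depends on an earlier observed outcome, here the 6-month result.

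The document makes this kind of dropout plausible. The Background says that "patients who develop acute exacerbations struggle to return to their previous level of exercise without professional guidance". The Results paragraph of the Abstract expects usual care to decline and the intervention arm to be maintained. The Intervention section gives a case manager only to the intervention arm. Loss related to decline could therefore occur, and could differ by arm. If decliners leave usual care, the 12-month effect is understated; if they leave the intervention arm, it is overstated. Either way, the result would be reported as protected against missing data.

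**Working it through.** **Inputs from the article.** Difference 54 m, SD 86 m, type I error 0.05, power 80%, 40 per group, 15% to 20% noncompliance and loss to follow-up combined, 100 recruited (Sample Size Calculation). Responses at 6 and 12 months with baseline as covariate (Data Analysis).

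**Inputs assumed.** The article gives no correlations between visits and no dropout mechanism. The main case uses correlations of 0.75 (baseline with 6 months), 0.65 (baseline with 12 months) and 0.75 (6 with 12 months).

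**Step 1: the plan's own figure.** For two independent groups, two-sided, n = 2 × (1.960 + 0.842)² × (86/54)² = 39.8, so 40 per group. Allowing for 20% loss, 40/0.80 = 50 per group, or 100. Both stated figures reproduce.

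**Step 2: how bias arises under independence.** After adjustment for baseline, the slope of the 12-month residual on the 6-month residual is (0.75 − 0.75 × 0.65)/(1 − 0.75²) = 0.2625/0.4375 = 0.60. With independence the 12-month mean is estimated from those who attend at 12 months, and their 6-month results are not used to correct it. If the completers in one arm have 6-month residuals averaging d metres above that arm as a whole, that arm's 12-month mean is too high by about 0.60 × d.

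The 6-month residual SD is 86 × √0.4375 = 56.9 m. The most extreme case is losing exactly the lowest fraction p of one arm, where d = 56.9 × φ(z_p)/(1 − p):

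- p = 0.15: 56.9 × 0.233/0.85 = 15.6 m; bias about 0.60 × 15.6 = 9 m.
- p = 0.20: 56.9 × 0.280/0.80 = 19.9 m; bias about 0.60 × 19.9 = 12 m.
- p = 0.26: 56.9 × 0.324/0.74 = 24.9 m; bias about 0.60 × 24.9 = 15 m.

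These are rough ceilings for one-arm dropout. Less sharp selection gives less bias.

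**Step 3: simulation at these correlations.** True effect 54 m, dropout depending on 6-month change. Estimated 12-month effect in metres (a dash means not run):

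| Arm where decline drives dropout | Missing | Independence | Exchangeable | Likelihood |
|---|---|---|---|---|
| Usual care only | 26% v 18% | 43 | – | 54 |
| Intervention only | same mechanism | 67 | – | 54 |
| Usual care only | 27% v 18% | 43.0 | 52.6 | – |
| Intervention only | same mechanism | 65.7 | 56.2 | – |
| Usual care only | 20% v 18% | 46–47 | 52 | 54 |
| Intervention only | same mechanism | 62 | 56 | 54 |
| Usual care only | about 18% in usual care | 48 | 52 | about 54 |
| Intervention only | same mechanism | 58 | 55 | about 54 |

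With the same rule in both arms, the independence estimate is 2 to 4 m too low. The one-arm bias under independence is mostly 6 to 13 m (54 − 48 up to 67 − 54), with one milder run at 4 m (58 − 54). The upper end comes from runs with 26% or 27% missing in usual care in the usual-care version, more than the plan anticipates.

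**Step 4: higher correlations and other mechanisms.** Correlations 0.7 to 0.9, overall dropout 15% or 20%, a 6-month difference of 27 m, and 400,000 simulated participants so that only bias remains:

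| Dropout depends on | Independence | Exchangeable | Likelihood |
|---|---|---|---|
| Nothing, or baseline only | about 54 | about 54 | about 54 |
| 6-month decline, both arms | 51–52 | about 54 | about 54 |
| 6-month decline, usual care only | 40–44 | 53–54 | about 54 |
| Unobserved 12-month decline, both arms | 45–48 | 48–51 | 48–51 |
| Unobserved 12-month decline, usual care only | 29–38 | 38–46 | 37–46 |

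In the third row, loss in usual care was 23% to 31%. The last two rows show that no structure, and no likelihood model, removes bias when dropout follows a value never observed.

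**The case against.** The strongest reply is that the large figures depend on two things the article does not say: an independence structure, and outcome-driven dropout confined to one arm. This stands. With only two response visits, an exchangeable structure is close enough to the truth to bring the one-arm bias down to about 2 m or less. It also stands that dropout depending only on baseline is already handled by the covariate, and that the 15% to 20% includes noncompliance, so actual loss may be lower. The Background statement on exacerbations concerns resuming exercise, not missed assessments; it makes the mechanism plausible without documenting it.

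Some stronger readings are tempting and are not supported:

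- A reader might infer that the primary test is seriously invalid. Under the null, one-arm dropout with independence did give a bias of about 11 m and a type I error of about 13%. With exchangeable, a comparable null run gave a bias of about 1 m. The article fixes neither condition, so these are worst cases.
- A reader might infer that the claim to use all data is false because a participant with neither follow-up visit contributes nothing. A mixed model with the same responses and baseline covariate leaves out the same participants, so this is no mark against the plan.
- A reader might infer from the repeated-measures ANOVA wording that incomplete cases will be dropped, as that method conventionally does. The phrase appears only in the sample-size rationale, and the Data Analysis section expressly keeps participants with incomplete follow-up. It is a clash of terms to be tidied.
- A type I error of 6.0% from uncorrected robust standard errors is too small to matter, and the article does not specify such errors.

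A condensed article may leave modelling detail to an analysis plan. That does not rescue this sentence, which asserts a protection and attributes it to the wrong thing.

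**Conclusion.** The concern holds in a limited form. The sentence is a misstatement, and the safety of the 12-month estimate turns on a covariance structure that the article leaves unnamed while presenting it as the safeguard. Under dropout driven by the observed 6-month outcome, the plausible bias on a 54 m effect runs from negligible (exchangeable) to a few metres (independence, same rule in both arms) and to roughly a tenth to a quarter of the effect (6/54 = 11%, 13/54 = 24%) for independence with one-arm dropout. These sizes rest on assumed correlations and dropout rules and on reading the model as an estimating-equation analysis. The 40 per group and the target of 100 do not change. Severity: should-fix.

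**What to change.** Make the primary analysis a likelihood-based (REML) mixed model for repeated measures. Use 6- and 12-month 6-minute walk distance as responses; group, visit, group-by-visit, baseline and baseline-by-visit as fixed effects; and an unstructured within-participant covariance. Name the 12-month group contrast as the primary test. Use the same form for the continuous secondary outcomes.

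Replace the working-covariance sentence with a statement that the model assumes data are missing at random. Bring the repeated-measures ANOVA wording in the Sample Size Calculation section into line with this model.

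Add one sensitivity analysis in which imputed 12-month values for dropouts are shifted downward, by arm, because neither approach cures dropout driven by the unobserved 12-month value.

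The cost is revised wording and a little more programming in standard mixed-model software, with no new data. The trade-off is reliance on a normal likelihood, which is reasonable for walk distance.

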#### Sample Size Calculation

Sample size calculations are based on the primary outcome measure, the 6MWT. We calculated sample size using a paired samples t-test. As the repeated measures analysis of the variance will be a more powerful analysis than a t-test, our sample size is a conservative estimate. Furthermore, as we will use baseline scores as a covariate in our planned analysis, we will be using within participant variability as our error (and not within participant variability), making our estimate even more conservative. A sample size estimation based on the knowledge of the differences in 6MWD that represent a clinically important difference (54 m and standard deviation of 86 m [15]), type I error of 0.05 and a power of 80%, revealed the need for a sample size of 40 in each group for a total of 80 participants. From our previous experience in this population, we estimate the rates of noncompliance and loss to follow-up to be 15% to 20% (8-10 participants per group). Therefore, we will aim to recruit 100 participants.

